# An experienced physiotherapist prescribing and administering corticosteroid and local anaesthetic injections to the shoulder in an Australian orthopaedic service, a non-inferiority randomised controlled trial and economic analysis: study protocol for a randomised controlled trial

**DOI:** 10.1186/1745-6215-15-503

**Published:** 2014-12-21

**Keywords:** Extended scope practice, Physiotherapy, Physical therapy, Orthopaedic, Shoulder, Corticosteroid injection, Economic

## Abstract

**Background:**

The early management of orthopaedic outpatients by physiotherapists may be useful in reducing public hospital waiting lists. Physiotherapists in Australia are prevented by legislation and funding models from investigating, prescribing, injecting and referring autonomously. This gap in service is particularly noticeable in the management of shoulder pain in early-access physiotherapy services, as patients needing corticosteroid injection face delays or transfer to other services for this procedure. This trial will investigate the clinical (decision making and outcomes) and economic feasibility of a physiotherapist prescribing and delivering corticosteroid and local anaesthetic injections for shoulder pain in an Australian public hospital setting.

**Methods/Design:**

A double-blinded (patient and assessor) non-inferiority randomised controlled trial will compare an orthopaedic surgeon and a physiotherapist prescribing and delivering corticosteroid injections to the shoulder. Agreement in decision making between the two clinicians will be investigated, and economic information will be obtained for estimating disease burden and an economic evaluation. The surgeon and the physiotherapist will independently assess patients, and 64 eligible participants will be randomised to receive subacromial injection of corticosteroid and local anaesthetic from either the surgeon or the physiotherapist. Post-injection, all participants will receive physiotherapy. The primary outcome measure will be the Shoulder Pain and Disability Index measured at baseline, and at 6 and 12 weeks post-injection. Analysis will be conducted on an intention-to-treat basis and compared to a per-protocol analysis. A cost-utility analysis will be undertaken from the perspective of the health funder.

**Discussion:**

Findings will assist policy makers and services in improving access for orthopaedic patients.

**Trial registration:**

Australia and New Zealand Clinical Trials Registry: 12612000532808 First registered: 21 May 2012. First participant randomized: 16 January 2013.

## Background

Patients referred to Australian public health orthopaedic services face lengthy waiting periods. Publicly accessible information on outpatient waiting times is scant and inconsistent. The Australian National Outpatient Care Database does not report waiting times
[1]. Queensland Health hospital performance data indicate that 54% of non-urgent outpatient referrals (not specifically orthopaedics) will take over a year to be seen
[2], and data from some hospitals reveal that the waiting time to see orthopaedic specialists may extend beyond 3 years
[3]. Furthermore, demands on orthopaedic services and subsequent waiting times are expected to worsen as the population ages
[4] and rates of obesity and arthritis increase
[5].

To combat future escalating delays for patients to access services such as orthopaedics, it has been proposed that the future health workforce should include greater role substitution and skill transference across professions
[6]. The early management of orthopaedic referrals by physiotherapists is one example. Physiotherapists have demonstrated high levels of agreement with orthopaedic surgeons in the diagnosis and management of orthopaedic conditions of the hip, knee
[7], and shoulder
[8]. Orthopaedic models of care involving extended scope physiotherapy practice have also reported reduced costs, reduced waiting times and improved health outcomes; however, the quality of this evidence to date is generally low
[9]. Corticosteroid injection by specially trained physiotherapists has been formally available in the UK since 2000 with a good safety record
[10]. Contemporary UK laws and service delivery models permit appropriately trained physiotherapists autonomy in areas of prescribing, injecting, investigation and referral. In contrast, physiotherapists in Australia are prevented by legislation from prescribing and administering medicines. They are also hindered in requesting radiologist injection or referring to other specialties by Medicare funding rules, which require that the request be made by a doctor. While early physiotherapist assessment of orthopaedic patients has been implemented in some Australian hospitals, patients in need of specific pharmaceuticals or invasive procedures such as injection are typically returned to waiting lists because their needs are beyond the scope of Australian physiotherapists. This presents a service gap in comparison to UK models of care, particularly with regards to some orthopaedic conditions such as subacromial impingement syndrome of the shoulder.

Shoulder pain is a common problem, with a population prevalence of 20 to 33%
[11], annual prevalence of 2.4% and an annual general practitioner (GP) care-seeking incidence of 1.5%
[12]. Subacromial impingement syndrome encompasses multifactorial pathology and is the most frequent cause of shoulder pain
[13]. Injection of corticosteroid and local anaesthetic to the subacromial space, sometimes combined with physiotherapy, is a common management strategy supported by clinical
[14–16] and economic evidence
[17–19]. The management of shoulder pain by Australian GPs is reported to be highly variable, often suboptimal and characterised by a high reliance upon specialist referral
[20]. Yet, despite shoulder pain being one of the most frequent orthopaedic conditions referred to physiotherapists working in early-access orthopaedic services in Australia
[21], these physiotherapists are unable to provide corticosteroid injection, resulting in delayed care for these patients. The capacity for injection delivery by physiotherapists in Australia may provide a solution; however, little is known of the clinical and economic outcomes of this model of care.

Existing literature concerning corticosteroid injection by physiotherapists is sparse and generally low quality. Positive health outcomes and the absence of adverse events have been reported; however, data are greatly limited to observational reports
[22–24]. No clinical trials have yet directly investigated corticosteroid injection by physiotherapists. Some information pertaining to corticosteroid injection by physiotherapists may be inferred from studies into physiotherapist-led orthopaedic models of care that have included physiotherapist injection amongst treatments provided. One unblinded randomised clinical trial utilised superiority statistics and reported that partially supervised physiotherapist care was not significantly different to that of junior orthopaedic doctors in terms of health outcomes or patient satisfaction, but hospital costs were lower because physiotherapists requested fewer X-rays. In this study, some participants in the physiotherapy group received corticosteroid injection but the study did not report the body region injected, nor whether the physiotherapist actually delivered the injection
[25]. Another unblinded (and non-randomised) clinical trial compared physiotherapist management of selected orthopaedic referrals to that of junior doctors and included physiotherapist corticosteroid injection as a treatment option. However, satisfaction and health outcome measures were not described and, again, the region of the injection was not reported
[26]. Physiotherapists delivered injections in a shoulder treatment trial
[27] but the efficacy of the physiotherapist as the provider of the injection was not investigated.

Therefore, the aim of this trial is to investigate the clinical and economic feasibility of a physiotherapist undertaking patient selection, and prescribing and delivering subacromial corticosteroid and local anaesthetic injection to the shoulder in an Australian public hospital setting. The primary aim of the study is to compare the clinical effectiveness of subacromial injection for shoulder pain, as delivered by a physiotherapist versus a consultant orthopaedic surgeon. Secondary study aims are to assess the agreement between the physiotherapist and orthopaedic surgeon in patient assessment and selection for injection, to estimate the economic burden of shoulder pain for patients awaiting orthopaedic care, and to calculate the costs of physiotherapist versus orthopaedic surgeon delivery of injections for shoulder pain. In our opinion, this is a novel and innovative study in that these research questions have not previously been investigated in a specific orthopaedic condition such as shoulder pain, in comparison to a consultant orthopaedic surgeon, or with a non-inferiority design. Furthermore, physiotherapist injection has not been previously reported in an Australian orthopaedic setting.

## Methods

### Design

A double-blinded (patient and outcome assessor) non-inferiority randomised controlled trial design will be used to compare injection decision and delivery by an orthopaedic surgeon to a model in which the physiotherapist makes the injection decision and gives the injection. Clinical decision-making between the two clinicians will also be compared. Economic data will be obtained for calculation of disease burden and a within-trial economic evaluation.

### Setting, process, inclusion and exclusion criteria

The study will take place at the Gold Coast Hospital and Health Service, with one upper limb staff specialist orthopaedic surgeon and one experienced physiotherapist who has prior training (in the UK) and experience in injecting and prescribing. A research assistant will identify appropriate orthopaedic referrals, contact potential participants, distribute study information, co-ordinate appointments and gain informed consent from participants for each part of the research. All participants will receive verbal and written information about the risks and benefits of participation and told that they can change their mind or withdraw at any time. Data will be stored in locked cabinets and password-protected digital files. Throughout the trial these will only be accessible by the research assistant and investigator (LB). The principal investigator will be given access at trial completion.

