**Process of recruitment, consent, randomization, treatment and measurement.**

#### Part Two, randomised controlled trial and randomisation process

Written informed consent for Part Two will be gained by the research assistant. Participants will then be randomised using concealed allocation to receive an injection from either the physiotherapist or the orthopaedic surgeon. The computer-generated randomisation sequence will be developed using Excel software by one investigator (LB) who will conceal the schedule from both the treating practitioners and the outcome assessor. Participants will be given a sealed opaque envelope by the research assistant, containing a standardised treatment sheet. This will direct the participant to one of two treatment rooms (Room A or Room B). The professional affiliation of the treating practitioner in each room will be unknown to both the study participants and the outcome assessor. Following participant randomisation to a treatment room (that is, a treating practitioner), the participant will provide written informed consent for the procedure before receiving the injection.

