#### Data and adverse event management

Adverse events reported by participants will be brought to the attention of the orthopaedic surgeon for clinical management as deemed appropriate. A Data Safety Monitoring Committee has been established comprising health service clinicians and experienced university academics, none of whom are involved in the study. Serious adverse events will be reported directly to both the Data Safety Monitoring Committee and the Human Research Ethics Committee. The biostatistician ([name]) will monitor the progress of the trial through interim statistical analyses at approximately one- and two-thirds completion. If the number of interim analyses is not small (for example, over five), the overall type I error rate could be controlled by adopting a higher level of significance for each interim statistical test
[40]. Alternatively, a more formal alpha spending function approach
[41] could be used to allocate some of the pre-specified overall type I error to each interim analysis. The interim analyses will be made available in confidence to the Data Safety Monitoring Committee and the Human Research Ethics Committee. The Data Safety Monitoring Committee will have authority to recommend trial cessation to the Sponsor.

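### One investigator both makes the allocation schedule and has access to the trial data during the trial, so outcomes can be linked to arms at any time

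*Protocol article*

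**What the plan says.** Four places in the Protocol article bear on this.

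- **Data access** (Setting, process, inclusion and exclusion criteria). Data sit in locked cabinets and password-protected files. "Throughout the trial these will only be accessible by the research assistant and investigator", the latter identified by initials. The next sentence reads: "The principal investigator will be given access at trial completion".
- **Allocation schedule** (Part Two, randomised controlled trial and randomisation process). "The computer-generated randomisation sequence will be developed using Excel software by one investigator", identified by the same initials. That person is to conceal it from two parties: the treating practitioners and the outcome assessor. The research assistant hands out sealed opaque envelopes, each holding a sheet that sends the participant to Room A or Room B.
- **Blinding** (Design). The trial is described as "A double-blinded (patient and outcome assessor) non-inferiority randomised controlled trial design".
- **Interim results** (Data and adverse event management). A biostatistician, whose name is removed from the text, analyses the data at about one-third and two-thirds of the way through. "The interim analyses will be made available in confidence to the Data Safety Monitoring Committee and the Human Research Ethics Committee".

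**The concern.** A non-inferiority trial is easier to defend when nobody involved in running it can see outcomes by arm before the data are complete. Two provisions suggest that the plan shares this aim: the principal investigator must wait for the data, and interim analyses go to oversight bodies in confidence. Giving the schedule and the data files to one person works against that aim, because the two together yield SPADI scores by arm without any interim analysis being run.

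What could suffer is judgement exercised while the trial runs or before the analysis is final. Examples are resolving data queries, deciding who counts as per-protocol (Data analysis sets that analysis beside intention-to-treat), choosing how to control interim type I error (Data and adverse event management only lists possibilities), and applying the conditional steps under Clinical efficacy. If the person making such a judgement knows the results by arm, a reader of the final report cannot rule out that the knowledge influenced it.

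**Working it through.** The point rests on role assignments, so the check sets the passages side by side.

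1. **Same person?** Yes. The data-access sentence and the randomisation-sequence sentence carry the same initials.
2. **Can outcomes be linked to arms?** Yes, by inference. The schedule gives the order of assignments, and the data files give participants and their outcomes. With 64 participants, joining the two is trivial. The article does not say that this investigator will do so.
3. **Does the text prevent it?** No. The concealment instruction covers the treating practitioners and the outcome assessor, and the Design section blinds the patient and the outcome assessor. This investigator is in none of these groups, and the article mentions no hand-over of the schedule, coded arms or separate custody.
4. **Would removing the schedule alone be enough?** Probably not. Other records plausibly reveal the arm: the Room A or Room B treatment sheet, the procedure consent taken after allocation, and the labour costs of the injecting clinician (Costs).
5. **Which routes to bias are closed?** Allocation concealment relies on sealed opaque envelopes and a schedule hidden from those who treat. The primary outcome is self-rated by participants who are blinded to profession. The article does not describe this investigator as treating, assessing or enrolling.
6. **Which routes stay open?** Data handling, per-protocol classification, and any interim or analysis choice in which this investigator takes part.
7. **Do any of the plan's figures change?** No. The sample size reproduces: with margin 15, SD 21.7 and one-sided alpha 0.05, a noncentral-t calculation gives 27 per group (power 0.806), so 54 in total, and 54 / (1 − 0.15) = 63.5, rounded up to 64. Separating the roles leaves this untouched.
8. **Can the effect be sized?** Not from the document. As a hypothetical only, suppose someone who knew the arm results picked the better of two one-sided 5% tests at the null boundary. The chance that at least one passes is 1 − Φ₂(1.645, 1.645; ρ), which is 7.5%, 6.8% and 6.3% for assumed correlations ρ of 0.8, 0.9 and 0.95.

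**The case against.** The strongest reply is that the article breaks no rule of its own. It blinds the patient and the outcome assessor, hides the schedule from the people whose knowledge could alter treatment or measurement, and lets one coordinating investigator manage the rest. It is also a condensed article; the full protocol may describe key custody or masked extracts. This largely stands. It limits the point to a role assignment that the article does state, and if the full protocol contains a safeguard, citing it resolves the matter.

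Four stronger readings are tempting, and the document does not support them.

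- **That interim confidentiality is breached.** The interim sentence names the two committees as recipients in confidence. It does not say that they are the only ones, and it does not bar investigators from data.
- **That the biostatistician is shut out of the data.** The biostatistician is not named in the data-access sentence, but the name is removed from the interim paragraph, so this could be the same investigator. Even if it is someone else, receiving an extract differs from access to the stored files. This calls for clarification and is not a proven contradiction.
- **That type I error rises to 6.3–7.5%.** That needs a role in analysis choices that no passage gives this investigator, and the correlations are assumed. Anyone choosing after seeing final unblinded data could do the same, so the figure does not measure the effect of access during the trial.
- **That the primary analysis is open to free choice.** Clinical efficacy fixes the model (GEE, first-order autoregressive working correlation, robust covariance) and the 15-point decision rule. Normality, missingness and post hoc steps follow stated conditions, so the room for judgement is narrow.

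**Conclusion.** The point holds in a limited form. As written, one investigator makes the schedule, by implication holds it, and has access to the outcome files throughout, so arm-level results are within reach at any time. This sits poorly with two other provisions of the same article without contradicting either. A reader might infer that the blinding or the allocation has failed; neither is shown.

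The size cannot be set. If this investigator takes no part in data, per-protocol, interim or analysis decisions, the cost is credibility alone. If they do, those decisions are exposed to knowledge of the results. The article neither states nor excludes such a part. The conclusion assumes that the matching initials denote one person, that the stored data include outcomes, and that no safeguard exists in a document not shown. It warrants a cheap improvement and does not threaten the trial's validity.

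**What to change.** - **Separate the roles from now on.** Keep the schedule, the participant-to-arm key and arm-identifying records such as room sheets with an existing team member who does not manage the outcome files, or with the biostatistician if that is a different person. The research assistant is not suitable, having access to the same files.
- **Mask the data holder.** Give the data-holding investigator only arm-masked data until the last 12-week visit is complete.
- **Fix the choices first.** Settle the per-protocol population and the conditional choices under Clinical efficacy before anyone who makes them sees arm-linked data. This matters most if the biostatistician holds the key, as the analyst is the person most likely to make those choices. If a fuller protocol or analysis plan already fixes them, cite it.
- **Clarify interim access.** State in the data-access paragraph how the biostatistician obtains data for the two interim analyses.
- **Record exposure to date.** Recruitment began in January 2013, so the change protects only the remaining conduct. Note whether anyone has already viewed arm-linked outcomes.

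The cost is transferring the key and the arm-identifying records, preparing masked files, and some changes of wording. No patients or visits are added, and the sample size is unchanged. The downside is that envelope queries and permitted unblinding must go through the new key holder.

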#### Part One and entry criteria for Part Two

Participants will be included in Part One, the initial assessment phase of the study, if they are aged 18 years and over, have a new referral from their primary care doctor to the hospital orthopaedic department for shoulder pain and have the ability to read trial literature (in English) and give consent. Participants will be excluded if they have prior knowledge of either the research physiotherapist or the research orthopaedic surgeon (for example, from previous interactions or consultation), or have had no X-ray of the shoulder in the past 12 months. Written informed consent for Part One will be gained by the research assistant, following which baseline demographic and outcome measure data will be collected. The orthopaedic surgeon and physiotherapist, blind to the other’s assessment and decision, will independently examine each participant and their completed assessment forms will be compared by the research assistant. The order of examination (orthopaedic surgeon or physiotherapist first) will vary according to clinician availability. Participants will be unaware of decisions made by their first assessor while being examined by their second assessor. In bilateral presentations the side requested in the GP referral will be addressed. In bilateral referrals both sides will be assessed, the participant asked to nominate their most troublesome side and practitioners will make same-day injection decisions for one side only. Participants will be eligible to enter Part Two of the study if there is agreement between the orthopaedic surgeon and physiotherapist on the question “would you provide subacromial injection today?” In addition, Part Two participants must be able fill in the questionnaires and follow post-injection instructions. If the clinicians disagree about injection or the side to be injected or both mark “no”, the participant will take no further part in the research and receive care as directed by the surgeon. Additional exclusion criteria for entry into Part Two includes previous surgery to the involved shoulder, current use of anticoagulant medication, the need for prophylactic antibiotics with the injection, pregnancy or breastfeeding. The flow of participants into Part One and Part Two of the study are demonstrated in Figure 
1.

